**Figure 3 F3:**
[figure not shown]
Schematic diagram of MRI limbus inversion degree measurement. “*l*” is the horizontal depth of the limbus insertion, and “*L*” is the horizontal depth of the ilium-acetabular roof. The degree of limbus inversion is *t* = *l/L *× 100%.

The application of MRI T1ρ mapping to assess the quality of the acetabular cartilage has been a research hotspot in recent years. MRI T1ρ mapping can quantitatively evaluate the proteoglycan content of articular cartilage and is a sensitive indicator for measuring proteoglycan content. The T1ρ mapping values are inversely proportional to proteoglycan content. The T1ρ mapping values of the anterior, superior, and posterior acetabular cartilage were measured on the sagittal planes passing through the medial third and the lateral third of the acetabular roof, respectively.
5.Avascular necrosis (AVN) of the femoral head was assessed based on the Kalamchi–MacEwen criteria.6.The initial magnitude of limbus inversion was measured using arthrography taken at closed reduction (Figure 4, same as the measurements on MRI).

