##### Statistical analysis

2.2.1.4.

Statistical analysis was performed using SPSS 27.0 software (IBM, SPSS Inc.).
1.To ensure consistency and reliability between multicenter research samples, it is first necessary to conduct a consistency analysis on the structural data, such as age and sex, of the included cases from each center and the International Hip Dysplasia Institute (IHDI) classification using the Cohen's kappa statistic. Simultaneously, the baseline characteristics (such as structural composition and pathological severity) of the included cohorts within each center must be consistent; imbalances in baseline characteristics were corrected by increasing the sample size.2.The included patients were divided into the non-limbus inversion group (A) and the limbus inversion group based on the presence of limbus inversion at closed reduction. The limbus inversion group was then further divided into the RLI group (B) and the resolved inverted limbus group (C) according to the state at final follow-up. A combination consisting of any two of the groups was organized into cohorts. Fisher's precision probability test was used to compare the difference between the sexes and affected sides, using analysis of variance to compare the different ages between the two groups. Differences in acetabular index was compared using Student's *t*-test. Chi-square test was used to compare IHDI classification, VAS and HHS, and Severin classification at the final follow-up, and analysis of variance was used to compare the MRI T1ρ mapping values and the difference in the initial magnitude of limbus inversion between groups B and C, as well as the difference between the initial magnitude of limbus inversion and that at the final follow-up in group B.3.ROC curve analysis was used to predict the cut-off value of the initial magnitude of limbus inversion in the case of persistent RLI as well as calculate its specificity, sensitivity, and statistical significance.4.Sample size calculation.In this study, ossification of the acetabular cartilage was the main observation; thus, improvement of the acetabular index was the most suitable observation indicator. The sample size calculation was based on the previously published acetabular index at the final follow-up in the group with RLI and the group without RLI after closed reduction (21.41°±3.61° and 18.88 ° ± 4.32° in the two groups, respectively) (15). The significance level *α*, the statistical power of the test, the ratio of the sample sizes in the two groups, and the percentage of patients lost to follow-up were set at 0.05, 0.9, 1:1, and 20%, respectively. The minimum sample size for each group was calculated to be 67 cases (134 cases in total). Therefore, at least 67 cases needed to be enrolled in the observation group and the control group, respectively.

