##### Prospective follow-up observation

2.2.2.3.

Prospective follow-up observation was performed for the two clinical cohorts, and frontal pelvic radiographs were reviewed every 6 months. Since development of the hip joint in children is a long-term process, the included pediatric patients needed to be followed until skeletal maturity. Data pooling was performed once every 2 years to compare the short-term and medium-term outcomes of hip joint morphological development between the two groups. MRI T1ρ mapping was used to quantitatively evaluate quality of the acetabular cartilage before and during postoperative follow-up. The evaluated aspects and parameters were the same as those specified in 2.2.1.

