##### Statistical analysis

2.2.2.6.

Fisher's precision probability test was used to compare the difference between the sexes and affected sides, using analysis of variance to compare the different ages between the surgical and non-surgical cohorts. Differences in acetabular index was compared using Student's *t*-test. Chi-square test was used to compare IHDI classification, VAS and HHS, and Severin classification at the final follow-up, and analysis of variance was used to compare the MRI T1ρ mapping values and the incidence of Grade III and Grade IV adverse events.

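### The randomised comparison of T1ρ in 2.2.2.6 does not use the baseline T1ρ already collected, and does not fix how six readings per hip enter the test

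*Protocol article*

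**What the plan says.** T1ρ is one of two secondary outcomes (2.3.2). Its measurement is set out in 2.2.1.3, item 4: "The T1ρ mapping values of the anterior, superior, and posterior acetabular cartilage were measured on the sagittal planes", these planes "passing through the medial third and the lateral third of the acetabular roof, respectively". Three regions on two planes make six readings per hip.

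For the randomised part, 2.2.2.1.2 has T1ρ measured by MRI in children who meet the eligibility criteria, before the article turns to allocation. Section 2.2.2.3 adds that "MRI T1ρ mapping was used to quantitatively evaluate quality of the acetabular cartilage before and during postoperative follow-up" and carries over the parameters of 2.2.1. A baseline value is therefore planned for both arms.

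The analysis is given in one clause of 2.2.2.6: "analysis of variance was used to compare the MRI T1ρ mapping values". The same choice of test appears in 2.2.1.4 and 2.2.3.4. None of the three sections names a baseline covariate, a summary value per hip, a within-hip term or a rule for the six sites.

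**The concern.** There are two separate issues.

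**Precision.** In a randomised comparison, a pre-treatment measurement of the same quantity is usually the most useful covariate available. The study pays for that MRI in every child, and the named test then leaves the value out. The comparison stays valid, but it is less precise than the data allow.

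**Unit of analysis.** Six readings from the cartilage of one hip are unlikely to be independent. Analysis of variance, with nothing more said, can be carried out in ways that respect this and in ways that do not. T1ρ is the only cartilage-quality measure among the listed outcomes. A spurious difference could be read as evidence that clearing the limbus restores cartilage, or that leaving it does harm.

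**Working it through.** **The plan's own figure.** The only design error rate in the article belongs to the acetabular index in part 1 (2.2.1.4). Significance level, power, allocation and loss "were set at 0.05, 0.9, 1:1, and 20%, respectively", with values of "21.41°±3.61° and 18.88 ° ± 4.32° in the two groups, respectively".
- Difference: 21.41 − 18.88 = 2.53. SD: √((3.61² + 4.32²)/2) = 3.98.
- n = 2 × (1.960 + 1.282)² × 3.98² / 2.53² ≈ 52.03, so 53 per group (two-sided, assumed).
- 53/0.8 = 66.25, so 67 per group. The stated figure reproduces.

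This calculation does not concern T1ρ. It is used below only to give a plausible 53 evaluable hips per group. The pooled result hardly depends on that number.

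**Baseline adjustment.** With baseline-to-follow-up correlation r, the variance of the adjusted group difference is about (1 − r²) times the unadjusted one. The article gives no r, so a range is assumed.

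| r | variance factor | reduction in variance | confidence interval narrower by |
|---|---|---|---|
| 0.3 | 1 − 0.09 = 0.91 | 9% | 1 − √0.91 ≈ 5% |
| 0.5 | 1 − 0.25 = 0.75 | 25% | 1 − √0.75 ≈ 13% |
| 0.7 | 1 − 0.49 = 0.51 | 49% | 1 − √0.51 ≈ 29% |

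**Unit of analysis.** Let ρ be the correlation between readings in one hip. It is not in the article, so it is assumed.
- *Six readings pooled as independent:* the variance is understated by the factor 1 + 5ρ, so the true error is 2 × [1 − Φ(1.96/√(1 + 5ρ))].
- *Six separate tests:* the chance of at least one p < 0.05 is 1 − 0.95⁶ = 26.5% if the sites are independent. For correlated sites it was simulated.
- *One mean per hip:* a single test on independent units.

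The simulations used no true difference, exchangeable normal readings and 53 hips per group, with 20,000 runs (6,000 at ρ = 0.1).

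| ρ | pooled, formula | pooled, simulated | at least one of six, simulated |
|---|---|---|---|
| 0.1 | 11.0% | 11.2% | 26.3% |
| 0.2 | 16.6% | 16.5% | 25.7% |
| 0.3 | 21.5% | 21.3% | 24.2% |
| 0.5 | 29.5% | 29.5% | 20.7% |
| 0.7 | 35.6% | 35.7% | 16.4% |

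The hip-mean test stayed close to 5% at every ρ (4.7% to 5.2%). A single site tested alone also stayed at about 5%.

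**The case against.** A reader might infer that the T1ρ false-positive rate in this study rises to something like 16% to 35%. The article does not support that, for four reasons.

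- It never says that the readings are pooled or that each site is tested. A mean per hip, or a repeated-measures analysis of variance with site as a factor, fits the same words and gives about 5%.
- A range of that kind mixes two quantities. The pooled figure is the error of one test. The six-test figure is the chance of any false positive across sites, while each test keeps its own 5%. Nothing in the article says that one significant site would count as success.
- Both figures rest on assumed correlations and exchangeable data. If the mean T1ρ differs by site, a pooled one-way test has a larger residual variance and rejects less often. Suppose ρ = 0.5 and the between-site variance is half the within-site variance. The ratio of true to assumed variance is then 3.5/1.5 = 2.33, and the rate is about 20% instead of 29.5%.
- The article is a condensed account. How regional readings are summarised is a detail that it may leave to a fuller plan.

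These objections stand against any claim that inflation is established, and taken alone the unstated unit of analysis would be a minor clarification. It can also be said that an unadjusted comparison of randomised groups is valid. That is true, but it does not answer the loss of precision. The article names both the baseline measurement and the test, and the test as named does not use the measurement. That can be improved whatever is decided about the six sites.

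**Conclusion.** The point holds as a choice of a weaker method than the collected data allow, together with an open unit of analysis. It is not a demonstrated error-rate failure. Leaving out baseline T1ρ gives up about 9% to 49% of the variance of the randomised comparison, if r lies between 0.3 and 0.7. The way the six readings enter the test decides whether the error rate is about 5% (one mean per hip), 11% to 36% (pooled, ρ from 0.1 to 0.7), or 5% per test with a 16% to 26% chance of at least one false positive (six tests, same range of ρ). All the correlations are assumptions. T1ρ is a secondary outcome, so the primary outcomes are unaffected.

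**What to change.** In 2.2.2.6, replace the analysis of variance for T1ρ with one of these:
- an analysis of covariance on the mean of the six sites per hip, with the baseline hip mean as covariate; or
- a mixed model with site as a fixed factor, a random hip or child effect, and baseline T1ρ as covariate.

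Report site-specific differences descriptively, with confidence intervals.

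In 2.2.1.4 and 2.2.3.4, use the same one-value-per-hip or mixed-model comparison without the covariate. Neither part describes a baseline T1ρ: part 1 takes it during follow-up, and part 3 schedules it at skeletal maturity.

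The cost is a wording change in three sections and a little more analysis work. No new data are needed. The study gives up significance claims for individual cartilage sites.

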#### Influence of inverted limbus clearance on acetabular development during DDH reduction: a multicenter prospective cohort study

2.2.3.

##### Research object

2.2.3.1.

In each center, the quality of reduction was first evaluated intraoperatively based on our published “safety and stability” criteria for an acceptable closed reduction (15), i.e., the safe zone >30° during intraoperative inspection and the reduction maintained with the hip in <65° abduction. DDH patients undergoing closed reduction at 6–18 months who satisfied the criteria were selected as participants for observation. The exclusion criteria are the same as those specified in study protocol 2.2.1. In the case of <70° abduction before DDH reduction, percutaneous adductor longus tenotomy was performed. The trail is illustrated in a flowchart as shown in Figure 6.

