##### Exclusion criteria

2.2.1.2.

1.Neuromuscular or syndromic DDH;2.Repeated surgical treatment because of re-dislocation, RAD, or other reason after DDH reduction;3.Incomplete imaging data.

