##### Selection of participants for the retrospective study

2.2.2.1.

To maximize the use of the peak ossification potential of acetabular cartilages in patients before the age of 5 years, pediatric patients who underwent successful closed reduction between 6 and 18 months that had experienced RLI and were ≤5 years old at follow-up were selected as study participants, given that it is more instrumental to observe the reversibility of delayed acetabular cartilage ossification. The frontal pelvic radiographs and MRI images of the hip joint were taken during follow-up to evaluate limbus inversion. The trail is illustrated in a flowchart as shown in Figure 5.

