###### Exclusion criteria

2.2.2.1.2.

Exclusion criteria 1–3 are the same as previously listed exclusion criteria 1–3 (2.2.1.2);
4. Patients who refused inclusion in the study cohorts.For pediatric patients satisfying the inclusion/exclusion criteria, the basic measures of acetabular development including the acetabular index and central-edge angle were assessed using frontal pelvic radiographs; the magnitude of limbus inversion, cartilaginous acetabular index, and T1ρ mapping values were measured using MRI.

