At present, the changes and outcomes of the inverted limbus after closed reduction of DDH remain controversial. Severin et al. (23) believed that after achieving stable closed reduction, the inverted limbus would be gradually absorbed and disappear; however, others believed that the inverted limbus was a key factor leading to AVN. Previous studies have been based on indirect observation of x-ray images, and there is a lack of direct evidence regarding the morphological evolution of the inverted limbus. This study used serial MRIs to observe the outcomes of limbus inversion after closed reduction of DDH, which lessened the impact of radiation on pediatric patients and enhanced the safety and reliability of the study. Our previous findings indicated that the magnitude of limbus inversion after closed reduction is closely related to its medium-term morphological outcome (16). However, the previous study had certain limitations since it was based on a small sample and did not follow-up until skeletal maturity. Previous studies have confirmed that a primary limbus inversion leads to primary acetabular dysplasia and early-onset OA (24, 25), but the long-term result of RLI has not been reported in DDH patients who previously underwent closed reduction.

Reaching skeletal maturity of the hip is a long-term process; therefore, the prospective design of this protocol better reflects the relationship between RLI and multiple prognostic outcomes while balancing many known or unknown biases. This research plan is to be led by the corresponding author's institution and carried out by multiple clinical research centers in cooperation with pediatric orthopedic centers in China. Compared to previous case-control studies, this study was designed as a multicenter clinical study with a higher level of evidence. Consistency of the characteristics included in a multicenter sample study is a key issue in clinical research. In the process of sample collection, cohort characteristics within each center are required to achieve homogeneity, which can be solved by increasing the sample size to ensure reliability of the final pooled samples. The follow-up rates in clinical studies are another key issue affecting reliability of the study results. Specialized staff in each center were assigned the task of following included cases, establishing case study databases, and recording various contact methods to guarantee a follow-up rate of over 80%.

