### Research ethics approval

4.1.

The registration of clinical trials was completed prior to this study protocol (registration number: ChiCTR1900020996) and was approved by the Medical Ethics Committee of Shengjing Hospital of China Medical University.

This study will recruit pediatric patients who have undergone closed reduction. Pediatric patients who meet al.l inclusion criteria and do not meet any exclusion criteria will be considered for this study. Prior to enrollment in the study, researchers will explain the objectives and content of the study in detail to the guardians of study participants as well as discuss the surgical risks and benefits of RLI clearance after closed reduction; researchers will ensure that the guardians are fully informed of the study. The guardians of the study participants must provide written informed consent before any research activity may begin. Participation in this study is voluntary and may be withdrawn by the participants' guardians at any time.

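### The prospective cohort (2.2.3) copies the retrospective exclusion for incomplete imaging with no time point, so enrolled and treated children can be removed for missing follow-up films

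*Protocol article*

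**What the plan says.** The protocol article describes three parts.

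- **Part 1 (2.2.1, retrospective cohort).** The third exclusion in 2.2.1.2 reads "Incomplete imaging data". It gives no time point and no list of images. The second exclusion in the same list is repeat surgery after reduction for re-dislocation, residual acetabular dysplasia (RAD) or another reason.
- **Part 2 (2.2.2, randomised).** Section 2.2.2.1.2 states: "Exclusion criteria 1–3 are the same as previously listed exclusion criteria 1–3 (2.2.1.2".
- **Part 3 (2.2.3, prospective cohort).** Section 2.2.3.1 states: "The exclusion criteria are the same as those specified in study protocol 2.2.1".

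Parts 2 and 3 then follow children radiologically every six months. For part 2, 2.2.2.3 says "frontal pelvic radiographs were reviewed every 6 months", and 2.2.3.3 sets the same interval for part 3. Both parts compare the acetabular index with Student's t-test (2.2.2.6, 2.2.3.4). Improvement of the acetabular index is a primary outcome (2.3.1).

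**The concern.** In a chart review, completeness of imaging can be judged when cases are selected, because follow-up has already happened. In a prospective cohort it cannot, if the term still covers follow-up films. A site or analyst who applies the copied rule with its part 1 meaning would drop children after grouping and treatment, on the basis of something that happened later.

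The two cohorts in part 3 receive different treatment: closed reduction in one, open reduction with limbus excision in the other. Attendance for films may depend on the cohort and on how the hip is doing. A comparison restricted to children with complete imaging could then differ from one among all children treated.

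**Working it through.** **Step 1. What imaging data means where the rule was written.** Sections 2.2.1.3 and 2.2.1.4 use follow-up pelvic radiographs, follow-up MRI with T1ρ mapping, and the arthrogram taken at reduction. Follow-up images are therefore part of the term in part 1.

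**Step 2. Which of these exist at entry to part 3.** Children are selected on intraoperative findings (2.2.3.1).

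| Image | Available at entry to part 3? | Basis |
|---|---|---|
| Pre-reduction radiograph | Yes, by implication | IHDI classification (2.2.3.4) and improvement in acetabular index (2.3.1) need one |
| Intraoperative arthrogram | Yes | Decides the cohort (2.2.3.2) |
| Six-monthly radiographs | No | 2.2.3.3 |
| MRI T1ρ at skeletal maturity | No | 2.2.3.3 |

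The criterion can be applied at entry to the first two rows. With its part 1 meaning it also covers the last two, which can be judged only after treatment. The text does not choose between these readings.

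**Step 3. Can the imported list be read purely as an entry screen?** The same sentence imports the exclusion for repeat surgery after reduction. In part 3 that can occur only after entry. Section 2.2.3.4 compares the re-dislocation rate and the incidence of RAD between the cohorts, so this exclusion would remove children who had the compared events and were re-operated for them. At least one item in the list is therefore a post-entry exclusion, and an entry-only reading of the imaging item cannot be taken for granted.

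**Step 4. Part 2.** The criteria stand under the selection of participants. For that stage, 2.2.2.1 says "The frontal pelvic radiographs and MRI images of the hip joint were taken during follow-up to evaluate limbus inversion". Section 2.2.2.1.2 continues "For pediatric patients satisfying the inclusion/exclusion criteria, the basic measures of acetabular development" and lists baseline measures, and randomisation follows in 2.2.2.2. This order favours a screen before randomisation.

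**Step 5. Does sample size drive the concern?** The only stated sample size belongs to part 1 (2.2.1.4) and reproduces.

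- Difference: 21.41 − 18.88 = 2.53°.
- Pooled variance: (3.61² + 4.32²)/2 = 15.847, so SD = 3.981°.
- n per group, two-sided α 0.05, power 0.90: 2 × (1.960 + 1.282)² × 15.847 / 2.53² = 52.03, rounded up to 53.
- With 20% loss: 53/0.8 = 66.25, rounded up to 67, as stated.

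Borrowing these inputs for part 3 is an assumption. With power = Φ(2.53/(3.981 × √(2/n)) − 1.96):

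| Analysed per group | Removed from 67 | Power |
|---|---|---|
| 67 | none | 95.7% |
| 54 | about 20% | 91.0% |
| 47 | about 30% | 86.9% |
| 40 | about 40% | 81.1% |

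Removal up to the planned 20% still leaves about 90% power. The issue is who is removed more than how many.

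**Step 6. Illustration of bias; every input except 2.53° is assumed.** If a fraction f of one cohort is removed and differs from those kept by d degrees, that cohort's mean shifts by f × d. With f = 0.20 and d = 2–3°, the shift is 0.4–0.6°, or 0.4/2.53 = 16% to 0.6/2.53 = 24% of the part 1 difference.

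On how many might be removed: if complete meant every six-monthly film and visits were independent, 95% attendance per visit leaves 0.95⁴ = 81%, 0.95¹⁰ = 60% and 0.95²⁰ = 36% complete after 4, 10 and 20 visits. At 98% attendance the figures are 92%, 82% and 67%. The document does not say that one missed film excludes a child, so these figures only show how strict that reading would be.

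**The case against.** - **The criteria belong to the eligibility stage.** Section 4.1 says that children who meet the inclusion criteria and "do not meet any exclusion criteria will be considered for this study". No section says that an enrolled child is removed for a missing film. A reader might infer that the plan orders such removal; the document does not support that. It supports only that the rule, as copied, allows it. For part 3 the repeat-surgery item weakens the pure-screen reading.
- **Entry images exist in part 3.** The arthrogram and a pre-reduction film give the criterion a workable meaning at enrolment. This stands. It would be wrong to say that the rule can act only later. But nothing in the text limits it to those images.
- **Part 2 is a pre-randomisation screen.** This largely stands. A reader might infer exclusion after randomisation, but the order of the sections points the other way.
- **Missed follow-up is treated as a retention matter.** The Discussion assigns staff "to guarantee a follow-up rate of over 80" per cent, and 2.2.1.4 allows for 20% loss. Neither calls it an exclusion. This stands, and shows that the authors may not intend removal.
- **Handling of missing data may sit in an analysis plan that is not shown, and the flow diagrams are not visible.** Silence on missing data is therefore not the point here. The point is a stated criterion that does not fit the design into which it was copied.
- **A t-test at a given time omits children without a film then in any case.** True, so the added effect of the criterion cannot be isolated.

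**Conclusion.** The point holds for part 3 as a drafting defect with a real analytic consequence. A retrospective exclusion was carried over with no time point, and its part 1 meaning includes images that do not exist at entry. It can therefore remove treated children for missing follow-up films, with a risk of selection bias in the acetabular index comparison. The repeat-surgery exclusion, imported by the same sentence, is a clearer case of the same defect. For part 2 a clarifying clause is a safeguard only.

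The size of any bias cannot be derived from the document. The 0.4–0.6° shift and the attendance figures rest on assumed fractions, differences and a strict definition of completeness, and should not be read as estimates. Whether bias arises at all depends on whether the rule is applied after entry and whether missing films relate to cohort and hip status.

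**What to change.** 1. In 2.2.3.1, replace the bare cross-reference with wording that limits the imaging criterion to the images needed for eligibility, grouping and baseline at entry. Add the same clause to 2.2.2.1.2 for clarity.
2. State that later missing films are missing data and that every enrolled or randomised child stays in the analysis. This also settles that repeat surgery after entry to part 3 does not remove a child from the comparison of re-dislocation and RAD.
3. Analyse the six-monthly acetabular index values, which are already collected, with a repeated-measures mixed model in place of Student's t-test. A child with some missed films then still contributes the others.

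The cost is one clause in each exclusion list and slightly more analysis work. The model relies on data being missing at random, an assumption weaker than the one needed to restrict the analysis to children with complete imaging. No extra visit or image is required.
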